**Fig. 1 f0005:**
[figure not shown]
Flow chart for the current study.

### Inclusion and exclusion criteria

2.3

In the current study, the following inclusion criteria will be used when assessing whether an individual can get access to psychological treatment:1)Over 18 years old of age.2)Can read and write in Swedish.3)Have access to a computer, tablet, or smartphone with an Internet connection.4)Have previously been diagnosed with ADHD.5)Are studying at a university or college in Sweden or working at least 50 % of a full time-employment.

The following exclusion criteria will be used:1)Shows elevated symptoms of depression or risk of suicide, i.e., a total score on the Patient Health Questionnaire – 9 items ((PHQ-9; Kroenke et al. (2001), >15 points, or scores >2 points on question i) concerning suicidality.2)Has started or changed their medication for any psychiatric diagnosis in the last three months.3)Exhibits another form of psychiatric diagnosis that requires more specialized care, for example substance abuse syndrome, anorexia nervosa, bipolar disorder, psychotic symptoms, or schizophrenia, as assessed with the MINI (Sheehan et al., 1998). There are no additional exclusion criteria for the qualitative studies regarding dropouts or participants that completed the treatment.

### Withdrawal

2.4

Participants can withdraw from the current study at any moment. The reason for this will be explored for research purposes, but the individual will be informed that he/she can defer from specifying her motive.

### Self-report measures

2.5

#### Adult Attention-deficit/hyperactivity disorder Quality-of-Life scale (AAQoL)

2.5.1

The AAQoL (Brod et al., 2015; Brod et al., 2006) is a disease-specific quality of life measure for adults with ADHD. The instrument measures quality of life-consequences of ADHD in four domains using and consists of 29 items. The instrument has excellent internal consistency (Cronbach's α = 0.93 for the overall measure). One example of an item is “In the last two weeks, how hard has it been for you to remember important things?”, scored on a five-point Likert-like scale from “Not at all/Never” (1) to “Extremely/Very Often” (5). The scale ranges from 0 to 100. The sum of the AAQoL is one of the two main outcomes measures in the study.

#### Adult ADHD Self-Report Scale-V1.1 (ASRS-V1.1) Symptoms Checklist (ASRS)

2.5.2

The ASRS is an instrument that measures ADHD-symptoms (Kessler et al., 2005). The instrument consists of 18 items that correspond to the 18 symptom-criteria for ADHD found in the DSM-IV-TR (Association, 2000). Of these 18 questions, six have been identified as most predictive of ADHD-symptoms. The overall range of the entire measure is 0 to 72. However, there are separate items focusing on attention and hyperactivity. The ASRS is the second main outcome measure of the study.

#### Generalized Anxiety Disorder – 7 Items (GAD-7)

2.5.3

The GAD-7 is an instrument that measures anxiety (Spitzer et al., 2006). Its internal consistency is excellent (Cronbach's α = 0.92), and it has good test-retest reliability (IntraClass Correlation = 0.83; Spitzer et al., 2006). The instrument includes seven items and has a single-factor solution. The score ranges from 0 to 21 points and the items range from 0 (“Not at all”) to 3 (“Nearly every day”; Spitzer et al., 2006). One example of an item is: “Over the last 2 weeks, how often have you been bothered by any of the following problems? Feeling nervous, anxious, or on edge.” (Item 1).

#### Patient Health Questionnaire – 9 Items (PHQ-9)

2.5.4

The PHQ-9 is a nine-item instrument measuring depression. It has excellent internal consistency (Cronbach's α = 0.89) and a good test-retest correlation (*r* = 0.84; Kroenke et al., 2001). The instrument has a single-factor solution. The score ranges from 0 to 27 points (Kroenke et al., 2001). Items range from 0 (“Not at all”) to 3 (“Nearly every day”). One example of an item is: “Over the last 2 weeks, how often have you been bothered by any of the following problems? Little interest or pleasure in doing things.” (Item 1).

#### Perceived Stress Scale (PSS)

2.5.5

The PSS is an instrument that evaluates the subjective experience of general stress in various situations and is scored on a five-point Likert-scale 0–4 (“Never” to “Very often”), with seven items being scored in reverse (items 4–7, 9–10, and 13). The PSS includes 14 items in total and has been shown to have good internal consistency (Cronbach's α = 0.84–0.86) as well as good convergent and discriminant validity (Cohen et al., 1983).

#### Negative Effects Questionnaire (NEQ)

2.5.6

The NEQ is a 32-item instrument that assesses unwanted and adverse events experienced by patients undergoing psychotherapy (Rozental et al., 2016; Rozental et al., 2019), e.g., “I experienced more unpleasant feelings” (Item 11). It is comprised of six factors: symptoms, quality, dependency, stigma, hopelessness, and failure. The internal consistency for the full instrument is excellent (Cronbach's α = 0.95), and is scored on several dimensions; 1) “Did you experience this?” (yes/no), 2) “If yes – here is how negatively it affected me”, from 0 (“Not at all”) to 4 (“Extremely”), and 3) “Probably caused by” (“The treatment I received” or “Other circumstances”).

### Treatments and therapists

2.6

The online treatment will be administered over ten weeks and consists of two mandatory modules and ten modules that can be selected from. The participants need to carry out the two mandatory modules and at least four additional modules that they have chosen to complete the treatment. The modules target different aspects of everyday functioning (e.g., how to plan your day and how to avoid losing things).

The intervention is inspired by the mechanisms of change in CBT for adult ADHD proposed by Ramsay (2010), including rudimentary mental scaffolding through psychoeducation, and ADHD-friendly environmental engineering to mitigate the consequences of executive dysfunction. The intervention is partly individualized through the therapist support, which also focuses on implementation strategies for participants to turn intentions into action (Ramsay, 2015). The therapists will have weekly check-ins with the patients in order to provide guided support. If a patient does not log in for a week the assigned therapist will send a SMS as reminder to log in and if the patient does not log in for two weeks, the assigned therapist will call the patient.

There are five basic modules to choose from and every basic module also has an advanced module (containing more tools and information) that can be selected after the completion of the basic module. The participants can choose a maximum of four basic modules and four advanced modules during treatment. See Table 2 for more information.

**Table 2 t0010:** Treatment content.

Basic treatment modules
Introduction module This module provides psychoeducation about ADHD and introduces the patient to the program.
“I have a hard time scheduling my time” This module focuses on planning and dealing with time in different ways to make it easier for everyday planning.
“I have a hard time maintaining everyday routines” This module focuses on establishing and maintaining routines to simplify everyday life.
“I often loose things” This module focuses on tools to help keep track and remember things, for example by categorization and organization. Work with acceptance is also a part of this module.
“I often feel stressed” This module focuses on strategies to better handle stress by both going back to our basic needs (food, sleep, and exercise) as well as looking at other skills and tools regarding stress.
“I have a hard time staying focused” This module focuses on attention and provides different tools to make it easier to maintain attention in different situations.
Exit module In the exit module, the treatment is summarized, and the patient creates a plan forward. The module also touches upon what to do if things get hard or the tools are forgotten.

The therapists will be university students undergoing basic clinical training in CBT during their final year at the Psychology Program at Uppsala University. They will have completed two to three semesters of clinical training when the current study is planned to commence. The therapists will receive a two-day training in the specific online CBT that will be administered in the study, provided by Psykologpartners W & W AB. The therapists will also receive weekly supervision by experienced clinical psychologists who developed the online intervention.

### Ethics and registration

2.7

The ethics application (Dnr. 2022-06261-01) was approved by the Swedish Ethical Review Authority and has been registered at ClinicalTrials.gov (NCT05700539). Participants will provide informed consent during the recruitment process. Great consideration will also be made to prevent participants faring worse by monitor their condition, i.e., deterioration in the control group is monitored by the researchers and deterioration in the treatment group is monitored by the therapists. Meanwhile unwanted and adverse events will be explored after treatment has ended.

### Statistical analysis

2.8

All outcomes will be analyzed using a series of ANOVAs, according to intent-to-treat-principle and missing values will be handled by using multiple imputation. Bonferroni-corrections to adjust for family-wise errors will also be used. The only exception applies to the NEQ which is only reported descriptively. Individual changes on the AAQoL and ASRS are determined using the Reliable Change Index (Jacobson and Truax, 1992; Maassen, 2004), i.e., yes/no, for improvement, deterioration, and non-response. For recovery, the Reliable Change Index and a positive change of two standard deviations in the direction of functionality will be used, i.e., criterion a (Jacobson and Truax, 1992). Given the large sample size that the study aims to recruit, moderation analyses are possible to conduct, but will be performed post hoc. Exploratory and confirmatory factor analyses will be used alongside reliability calculations (Omega) and analytic techniques used in Rasch analysis.

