## Abstract

Attention deficit hyperactivity disorder (ADHD) is a disorder characterized by hyperactivity, impulsivity and lack of attention. It can have a major impact on everyday life and result in negative consequences for one's personal, academic, and work situation. For individuals with symptoms of ADHD, increased levels of anxiety and depression are common, and an overall reduction of quality of life is often present. This study protocol describes a clinical trial of internet-based cognitive behavioral therapy (iCBT), using a randomized controlled study design, with the primary aim to increase quality of life, as well as to reduce symptoms of ADHD, anxiety, depression, and stress. A second aim is to investigate, by qualitative means, what aspects of treatment were perceived as helpful and hindering when it comes to completing iCBT. Two hundred participants with symptoms of ADHD will be included and randomized to two conditions (treatment and wait-list control). The treatment period is comprised of a maximum of ten weeks, with two mandatory modules and ten modules from which the participants can choose freely. Self-report measures will be completed by the participants at baseline and end of treatment, as well as at a six-month follow-up. The treatment is guided by therapists and consists of weekly correspondence with the participants. The study will utilize an intention to treat design, with ANOVAs and Reliable Change Index to evaluate treatment effects. The qualitative part of the project will be interview-based and employ thematic analysis. Lastly, a psychometric evaluation of a common instrument for determining ADHD-symptoms will also be made. The results will hopefully contribute to the evidence base for iCBT for individuals with symptoms of ADHD and help disseminate potentially effective interventions.

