### Research questions

1.2

•What are the group-average outcomes of the online intervention at the end of treatment and at a six-month follow-up?•How many individuals experience a reliable change when it comes to ADHD-symptoms and quality of life at the end of treatment and at a six-month follow-up?•Did the participants experience any negative consequences in relation to the online intervention?•How do participants who have discontinued treatment view the online intervention and their participation?•How do people who have undergone the entire treatment (≥ six modules) perceive the online intervention and their participation, both in terms of helping and hindering aspects?•What are the psychometric properties of the Swedish translation of ASRS in a Swedish population?

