### Participants

2.2

A power analysis was conducted using G*Power 3.1 to ascertain the number of participants needed to detect differences at post treatment and follow-up. The sample size calculation was based on three time points: pretreatment, post treatment, and at a six-month follow-up for both groups. The anticipated effect size of the treatment was set to Cohen's d 0.1 and the analysis used was a repeated measures ANOVA with Tukey's post hoc test. The randomization is carried out via www.random.org using space noise a randomization principle. The allocation will be into two groups: treatment and waitlist control group. No concealment procedure was used since the participants in the control group were informed that they would receive treatment at a later stage. The low effect was set based on the fact that this type of treatment has not been thoroughly researched and several existing studies have demonstrated a small effect. As a result, the number of participants needed was 138, but it was decided to include 200 participants to account for an expected high dropout rate. As for the qualitative studies, twelve to fifteen participants for each study will be interviewed, which is regarded as adequate to achieve code saturation in the qualitative analysis (Hennink et al., 2017). In terms of the psychometric evaluation of the ASRS (Study 5), two hundred participants are considered sufficient for determining internal consistency, convergent and divergent validity with other self-report measures, and to conduct exploratory and confirmatory factor analyses. See Fig. 1 for a flow chart over the recruitment process.

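### The planned repeated measures ANOVA uses the baseline score as a time level instead of a covariate and names no between-arm contrast at post-treatment or six months; it is valid, but less precise than the data allow

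*Protocol article*

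**What the plan says.** Section 2.8 (Statistical analysis) sets one method for every outcome except the NEQ, which is only described: "All outcomes will be analyzed using a series of ANOVAs, according to intent-to-treat-principle and missing values will be handled by using multiple imputation". Bonferroni corrections are added. No covariate, ANCOVA or mixed model is mentioned.

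Section 2.2 (Participants) gives the form of the ANOVA through the power calculation: "the analysis used was a repeated measures ANOVA with Tukey's post hoc test". It adds: "The sample size calculation was based on three time points: pretreatment, post treatment, and at a six-month follow-up for both groups". Pretreatment is therefore one of the three levels of time.

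The target is stated twice. Section 1.2 asks: "What are the group-average outcomes of the online intervention at the end of treatment and at a six-month follow-up". Section 2.2 says the trial was sized "to ascertain the number of participants needed to detect differences at post treatment and follow-up". Both name two visits and give them equal standing.

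Table 1 shows all five analysed scales (AAQoL, ASRS, GAD-7, PHQ-9, PSS) collected at baseline, and section 2.1 has these scores submitted at sign-up, before allocation. They are therefore proper pre-randomisation covariates.

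**The concern.** With two arms and three time points, the group-by-time test has (2 − 1)(3 − 1) = 2 degrees of freedom. A significant result says that the two profiles differ somewhere. It gives neither the arm difference at the end of treatment nor that at six months, which are the quantities the article asks about.

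Treating baseline as a level of time also amounts, for any one later visit, to comparing change from baseline. Change subtracts the baseline score with a weight of exactly one, whereas adjustment uses the weight that the data support. Unless the correlation is 1, change has the larger variance. If the ANOVAs are instead run on the post scores alone, the baseline score is not used at all.

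At stake is the width of the confidence intervals for the two main outcomes (AAQoL and ASRS), and whether the reported result answers the stated question.

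**Working it through.** **The plan's own figure.** Section 2.2 reports: "the number of participants needed was 138, but it was decided to include 200 participants to account for an expected high dropout rate". Taking the stated 0.1 as the ANOVA effect size f, with three time points, two groups, and assumed alpha 0.05, power 0.80 and correlation 0.5, the group-by-time test needs 164 participants and has 73% power at 138. The figure 138 comes out with four measurements, or with three if the correlation is about 0.58. That is a separate matter. Here 138 serves only as 69 per arm in an illustration.

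**Inputs.** From the article: two arms, three time points, baseline collected on all analysed scales, 138 needed and 200 planned. Not in the article, so assumed: 1:1 allocation, two-sided alpha 0.05, equal SDs at all visits, and r from 0.3 to 0.8.

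**Variance of the arm difference at one visit**, in units of 2σ²/n with n per arm:
- post score alone: 1
- change from baseline (the group-by-time contrast for that visit): 2(1 − r)
- baseline-adjusted: 1 − r²

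Reduction from adjustment:
- against change: 1 − (1 − r²)/[2(1 − r)] = 1 − (1 + r)/2 = (1 − r)/2
- against the post score: r²

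| r | against change | against post score |
|---|---|---|
| 0.3 | 35% | 9% |
| 0.4 | 30% | 16% |
| 0.5 | 25% | 25% |
| 0.6 | 20% | 36% |
| 0.7 | 15% | 49% |
| 0.8 | 10% | 64% |

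A simulation (4,000 trials, 69 per arm) gave a ratio of adjusted to change variance of 0.74, 0.80 and 0.86 at r = 0.5, 0.6 and 0.7. The formula (1 + r)/2 gives 0.75, 0.80 and 0.85.

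In participants, with 200 randomised the change contrast carries the information of an adjusted analysis on 200 × 0.75 = 150 (r = 0.5) to 200 × 0.85 = 170 (r = 0.7).

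**Illustration in power.** The effect is an assumption. Section 2.2 says: "The anticipated effect size of the treatment was set to Cohen's d 0.1". If 0.1 is read as f for the interaction, and the effect δ is the same at both later visits, the interaction terms are −δ/3, δ/6 and δ/6. Then f = δ/√18, so δ = 0.1 × 4.243 = 0.424 SD. With r = 0.5, one visit, alpha 0.05 and the normal approximation:

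- 69 per arm, change: SE = √(2/69) = 0.170; 0.424/0.170 = 2.49; power 70%
- 69 per arm, adjusted: SE = √(2/69 × 0.75) = 0.147; 0.424/0.147 = 2.88; power 82%
- 100 per arm, change: SE = √(2/100) = 0.141; power 85%
- 100 per arm, adjusted: SE = √(2/100 × 0.75) = 0.122; power 93%

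If Bonferroni splits alpha over the two visits (0.025 each, critical value 2.24), the figures at 69 per arm become Φ(2.49 − 2.24) = 60% and Φ(2.88 − 2.24) = 74%. The gain remains.

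**The case against.** **The article foresees more than a bare omnibus test.** This stands. A reader might infer from section 2.8 alone that the ANOVAs ignore baseline and stop at an overall test. Section 2.2 shows otherwise: baseline is a level of time, and Tukey comparisons follow. But the contrasts of interest are not singled out among the pairs, and section 2.8 names Bonferroni and not Tukey. A pairwise comparison of the two arms at one visit is also a comparison of post scores, so it does not recover the baseline information.

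**The size of the loss is not in the documents.** This stands too. No correlation, alpha or power is stated, so no single percentage can be given as fact.

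**The omnibus test may not be weaker.** A reader might set its 73% power at 138 participants against the 82% of the adjusted contrast. That is not like for like: the first tests both visits jointly, the second one visit at full alpha. With alpha split over two visits, the adjusted contrast has 74% per visit, so the gain over the omnibus test nearly vanishes in that example. The fair comparison is one visit against the same visit, 70% against 82%.

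**The trial has room.** A reader might infer that the sample cannot bear the loss. Section 2.2 plans 200 against 138 needed, which allows for 62/200 = 31% dropout, so the point does not rest on a tight sample.

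**The group main effect would be diluted by baseline.** It would, but the article does not nominate that effect as the treatment test, so nothing is charged to it.

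**Covariates and contrasts belong in an analysis plan that is not shown.** This is partly right: leaving the contrasts to that plan would be no fault in itself. The ANOVA, however, is a stated choice, and an analysis plan that followed it would inherit the inefficiency.

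**Conclusion.** The point holds as one of efficiency and clarity of target. With randomised arms, the planned repeated measures ANOVA is valid, and no bias is shown; a reading that the analysis is wrong would go beyond the text. What can be said is that the stated method uses the collected baseline scores less well than it could, and that it does not lead directly to the two arm differences the article asks about.

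In large samples, adjustment is more precise than the change contrast at every r below 1, and than post scores at every r above 0. The size depends on an unstated correlation: 35% to 10% of the variance against change for r = 0.3 to 0.8, and 9% to 64% against post scores. The power figures rest further on the assumed 0.42 SD effect, equal SDs, 1:1 allocation and complete data. The change is worth making because it costs no participants in a trial that expects high dropout.

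**What to change.** In section 2.8, replace the series of ANOVAs with wording such as:

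*Each outcome except the NEQ will be analysed with a linear mixed model for the post-treatment and six-month scores, with arm, visit, arm × visit, baseline score and baseline × visit, and an unstructured covariance between visits. All randomised participants are analysed as allocated. The adjusted between-arm difference with its confidence interval will be reported at post-treatment and at six months, under the planned Bonferroni correction.*

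An ANCOVA at each visit within the planned multiple imputation would serve equally well if the authors prefer to keep imputation as the main method for missing data. Both visits keep the equal standing they have now.

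The cost is a change of wording, preferably before outcome data are seen, and slightly more modelling. No new data, visits or participants are needed.

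### Tukey in the sizing and Bonferroni in the analysis are not reconciled, no adjusted alpha is shown, and on the natural reading the two main outcomes share alpha with three secondary scales

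*Protocol article*

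**What the plan says.** **Sizing (Protocol article, Participants).** "The sample size calculation was based on three time points: pretreatment, post treatment, and at a six-month follow-up for both groups". The effect size is given as follows: "The anticipated effect size of the treatment was set to Cohen's d 0.1". On the test, "the analysis used was a repeated measures ANOVA with Tukey's post hoc test". The result is that "the number of participants needed was 138, but it was decided to include 200 participants to account for an expected high dropout rate". The section gives no alpha, power or correlation.

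**Analysis (Statistical analysis).** Every outcome goes into a series of ANOVAs under intention to treat with multiple imputation. Then: "Bonferroni-corrections to adjust for family-wise errors will also be used. The only exception applies to the NEQ which is only reported descriptively". Tukey is not mentioned here, and the tests that make up the Bonferroni family are not listed.

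**Hierarchy.** The AAQoL section states: "The sum of the AAQoL is one of the two main outcomes measures in the study". The ASRS section names the ASRS as the second. Table 1 lists six instruments; without the NEQ, five remain to be tested (AAQoL, ASRS, GAD-7, PHQ-9, PSS). The abstract describes the trial "with the primary aim to increase quality of life, as well as to reduce symptoms of ADHD, anxiety, depression, and stress", which places all five constructs under one primary aim.

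**The concern.** Two sections name two different multiplicity procedures and neither refers to the other. With two arms, Tukey has nothing to correct between arms at a single time point. If it ran over all six arm-by-time cells it would cover C(6,2) = 15 pairs, of which only two (post-treatment and six months) compare randomised arms after baseline. Tukey therefore does not describe the comparisons that matter most, and Bonferroni as written does not say what it divides by.

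If the family is all five tested scales, each main outcome is judged at 0.05 / 5 = 0.01 instead of 0.05 / 2 = 0.025. Scales that the protocol does not call main outcomes then reduce the power of the two that it does. The sizing does not show that either divisor was allowed for. Leaving the family open also leaves the threshold for a positive result open.

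**Working it through.** **Inputs from the protocol:** two groups, three time points, 138 needed, 200 to be included, effect size written as d 0.1, five tested scales, two main outcomes.

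**Assumptions, not in the protocol:** equal allocation; d 0.1 was entered as f = 0.1, the effect-size metric that G*Power uses for repeated measures ANOVA; the tested effect is the group-by-time interaction; sphericity holds (epsilon 1); correlation r is 0.5 to 0.58.

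**Formula.** Noncentral F with λ = f² × N × m / (1 − r), df1 = (k − 1)(m − 1), df2 = (N − k)(m − 1), where k = 2 groups and m = 3 time points. So df1 = 2, and df2 = 272 at N = 138 or 396 at N = 200.

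**Step 1: the plan's own figure.** With f = 0.1, r = 0.5, alpha 0.05 and 80% power, the required N is 164, not 138. With three time points, 138 comes out at r = 0.58. It also comes out at r = 0.5 with four measurements, but the protocol states three. The range r = 0.5 to 0.58 therefore runs from a conventional value to the value at which 138 gives 80% power.

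**Step 2: noncentrality.**
- N = 138: λ = 0.01 × 138 × 3 / 0.5 = 8.28 at r = 0.5; 4.14 / 0.42 = 9.86 at r = 0.58.
- N = 200: λ = 6 / 0.5 = 12.0 at r = 0.5; 6 / 0.42 = 14.29 at r = 0.58.

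**Step 3: power.**

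| N | r | alpha 0.05 | alpha 0.025 (two outcomes) | alpha 0.01 (five outcomes) |
|---|---|---|---|---|
| 138 | 0.5 | 72.8% | 62.8% | 49.7% |
| 138 | 0.58 | 80.5% | 71.8% | 59.6% |
| 200 | 0.5 | 88.1% | 81.5% | 71.4% |
| 200 | 0.58 | 93.1% | 88.6% | 80.9% |

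The 138 rows describe the case in which 1 − 138/200 = 31% of participants supply no usable outcome. The 200 rows describe no loss.

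**Step 4: what the choice of family costs.** The gain from two outcomes over five is 62.8 − 49.7 = 13.1 and 71.8 − 59.6 = 12.2 points at 138, and 81.5 − 71.4 = 10.1 and 88.6 − 80.9 = 7.7 points at 200. That is about 8 to 13 points.

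**Step 5: N for 80% power.** At alpha 0.025 it is 194 (r = 0.5) or 164 (r = 0.58). At alpha 0.01 it is 234 or 198.

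**Step 6: was an adjusted alpha used in the sizing?** This cannot be settled. With f = 0.1, three time points and 80% power, N = 138 also arises at alpha 0.01 with r = 0.71. At alpha 0.025 with r about 0.65 the required N is 136, close to 138.

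**Step 7: sensitivity to the effect-size metric.** For two groups f = d/2, so a literal d of 0.1 is f = 0.05. At N = 138 and r = 0.5, power is then 23.0% at alpha 0.05, 15.2% at 0.025 and 8.6% at 0.01.

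**The case against.** The strongest reply has four parts.

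- **The procedures can coexist.** Tukey could serve pairwise post hoc contrasts within one ANOVA while Bonferroni covers several ANOVAs. This stands. A reader might infer that the two sections contradict each other, but the text shows only that they are not reconciled.
- **The five-scale family is an inference.** The NEQ exception may simply exempt that instrument from inferential testing and say nothing about the Bonferroni divisor. This stands in part: five scales is the natural reading, because the exception follows directly on the Bonferroni sentence and the paragraph covers all outcomes, but it is not stated.
- **The sizing may already allow for multiplicity.** A reader might infer that 138 comes only from an uncorrected alpha of 0.05. Step 6 shows otherwise. What can be said is that no adjusted alpha is shown.
- **The planned number is 200, and the detail may sit elsewhere.** A reader might take 50% to 63% at 138 as the loss caused by Bonferroni. It is not: on the same inputs (r = 0.5) power is already 73% without correction, so Bonferroni accounts for 10 to 23 points of the drop. The 138 rows also apply only at 31% loss, and people who stop treatment are still asked for the post-treatment survey. Exact alpha splits are often left to an analysis plan, and the two main outcomes are named in advance. Even so, the article itself fixes a test for the sizing, a different correction for the analysis, and a primary aim wider than its main outcomes. Those statements need aligning wherever the detail sits.

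**Conclusion.** The point holds as a failure to reconcile and define. The sizing names Tukey, the analysis names Bonferroni, the family is not given, no adjusted alpha is shown, and the abstract's primary aim covers five constructs where the measures sections name two main outcomes.

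Its size is conditional on f = 0.1, the interaction test and r between 0.5 and 0.58. On those assumptions, moving from a five-outcome to a two-outcome family is worth about 8 to 13 points of power for each main outcome. With 200 analysed, a two-outcome family keeps power above 80% across the range. A five-outcome family does so only at the upper end.

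The documents do not support a single figure for power lost to multiplicity, nor the statement that multiplicity was ignored in the sizing. Whether d 0.1 was meant as f is a separate and larger question, and every absolute figure here depends on it.

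**What to change.** 1. Delete the Tukey reference in the Participants section, or say which comparisons it covers and how it relates to Bonferroni.
2. State in the Statistical analysis section that the confirmatory family is the AAQoL and ASRS totals, tested with Holm at a two-sided family-wise 0.05 on one pre-named contrast or time point. The sponsor should choose it, because the research questions give post-treatment and six months equal standing.
3. Report GAD-7, PHQ-9 and PSS as secondary, with confidence intervals, outside that family.
4. Align the abstract's primary aim with the two main outcomes.
5. Restate power at alpha 0.025 for the chosen test, showing the effect-size metric, correlation, alpha and power. This figure is conservative for Holm, which tests the second outcome at 0.05 once the first is rejected. If a single contrast replaces the interaction test, the powers above do not carry over and must be recalculated.

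The cost is wording and one recalculation. The small downside is that the secondary scales carry no confirmatory claim.
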